#### Secondary outcome

The secondary outcomes of this study will assess ODI score at additional time points, VAS, SF-36, EQ-5D, radiological indicator (DH, LL angles and vertebral fusion rate) and hospitalisation information. The data collection schedule is presented in table 2. For those who cannot come for follow-ups, our research assistant will contact them by phone or email to complete the questionnaire.

**Table 2 T2:** The time schedule for collection of data for this trial

	Day≤−1	Day1	Day2–29	Day30±7 days	Day90±7 days	Day180±7 days	Day360±7 days
Inclusion and exclusion criteria	**√**						
Signing of informed consent form	**√**						
Demographic assessment	**√**						
Physical examination	**√**						
Operation time/Intraoperative blood loss		**√**					
Serum CK/CRP			**√**				
Length of stay			**√**				
ODI score	**√**			**√**	**√**	**√**	**√**
VAS score	**√**			**√**	**√**	**√**	**√**
SF-36-PF	**√**			**√**	**√**	**√**	**√**
SF-36-BP	**√**			**√**	**√**	**√**	**√**
QoL EQ-5D	**√**			**√**	**√**	**√**	**√**
Disc height	**√**				**√**	**√**	**√**
Lumbar lordosis angles	√				√	√	√
Vertebral fusion rate							**√**
Complications		**√**	**√**	**√**	**√**	**√**	**√**
Adverse events		**√**	**√**	**√**	**√**	**√**	**√**

√, This refers to the data collection at the scheduled time.

BPbody painCKcreatine phosphokinaseCRPC reactive proteinEQ-5DEuroQol 5 DimensionsODIOswestry Disability IndexPFphysical functioningQoLquality of lifeSF-3636-Item Short Form SurveyVASVisual Analogue Scale

#### ODI score

The ODI scores were assessed at 1 month, 3 months and 6 months postoperatively. Scores are determined following the aforementioned method.

#### VAS score

The VAS score records an individual’s self-rated health status on a vertical VAS, which was assessed at 1 month, 3 months, 6 months and 12 months postoperatively. A 10 cm ruler with 10 gradations marks the pain scale, with 0 for no pain and 10 for the worst, unbearable pain. Higher scores equate to more severe pain.^24^

#### SF-36 questionnaire

SF-36 questionnaire is used to evaluate health-related quality of life. The evaluation covers eight specific domains: physical functioning (PF), role-physical, body pain (BP), general health, vitality, social functioning, role-emotional and mental health. The main statistical indicator of SF-36 is to calculate the health score of eight dimensions. The initial score of each dimension is equal to the sum of the scores of all items within each, higher score on the SF-36 reflects superior health status.^25^ In this study, we focus on two aspects: PF and BP, conducted at 1 month, 3 months, 6 months and 12 months postoperatively.

#### EQ-5D questionnaire

The EQ-5D health scale features a descriptive system and EQ-VAS. The descriptive system encompasses five dimensions, including mobility, self-care, usual activities, pain/discomfort and anxiety/depression. Each of the five items is scored from 1 to 5. The EQ-VAS, a 20 cm vertical scale, ranges from 0, indicative of the poorest health state, to 100, reflective of optimal health.^26^ Participants are required to pinpoint their health status on this scale, offering a snapshot of their well-being on the survey day at 1 month, 3 months, 6 months and 12 months postoperatively.

#### Radiological indicators

DH and LL angles are measured by X-rays. The reduction in DH correlates with the progression of intervertebral disc degeneration, characterised notably by intervertebral space stenosis. Thus, the magnitude of DH reduction serves as an indicator of the degenerative process’s severity. LL angles over 10° suggest progression risk in spondylolisthesis. The approach to measurement is meticulously detailed in the prior section. An experienced spine physician and radiologist with ten years of experience will simultaneously evaluate the intervertebral fusion of the subjects based on CT scans. The fusion criteria are shown in table 3.^27^

**Table 3 T3:** Bridwell intervertebral bone graft fusion evaluation system

Grade	Description
I	Fused with remodelling and trabeculae present
II	Graft intact, not fully remodelled and incorporated, but no lucency present
III	Graft intact, potential lucency present at top and bottom of graft
IV	Fusion absent with collapse or resorption of graft

#### Information during hospitalisation

Information during the hospitalisation includes operation time, hospital stay, intraoperative blood loss, serum creatine phosphokinase (CK) and C reactive protein (CRP) level. Serum levels of CK and CRP will be collected within 2 days after receiving the surgery, which serves as a crucial measure to delineate the extent of soft tissue trauma experienced during the surgical procedure

### Data collection, management and monitoring

The data safety monitoring committee (DSMC) will be composed of two expert spine surgeons and an expert statistician. Efficacy and safety data for all patients will be reviewed throughout the study. A standard data collection and management system including CRF and electronic data capture will be adopted. CRF data filling and management will be carried out by research assistants who are blinded from the study. All participant identities and recorded data will be kept confidential, and only the principal investigator and DSMC will have access to the data for this study. The names of subjects will not be identified in any publications from this study.

According to the data collection schedule (table 1), data will be collected before surgery, on 2 days, in 1 month, 3 months, 6 months and 12 months after the surgery.

### Statistical analysis

In this study, three analysis sets will be required. For the safety analysis set, any adverse event (AE) will be recorded from patients who have undergone UBE-TLIF or MT-TLIF following randomisation. In the full analysis set, all participants who were randomised to the surgical intervention and for whom complete data sets were accessible after randomisation. In instances of missing data, we employed the last observation carried forward and baseline observation carried forward methods for imputation. For the per-protocol cohort, at least 90% of subjects should fulfil the following criteria: (1) receive either UBE-TLIF or MT-TLIF treatments; (2) with no violation of the protocol; (3) complete the full follow-up and (4) obtain all required data. Continuous variables, including VAS score, ODI score, operation time, intraoperative blood loss, serum CK and CRP level, DH, LL, SF-36, QoL EQ-5D as well as hospital stay, will be expressed as means±SDs, while categorical data, including vertebral fusion rate, will be shown as frequencies. The independent t-test and Pearson χ^2^ will be applied to analyse continuous and categorical variables, respectively. If indicated, statistical analysis between subgroups will be performed. All statistical analyses will be performed using Statistical Product and Service Solutions (V.26.0, IBM) by the principal biostatistician. A p<0.05 (two sided) will be considered statistically significant.

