### Study design and settings

This is a prospective, randomised, controlled, non-inferiority clinical study. A total of 96 eligible patients will be randomly assigned to the MT-TLIF arm or UBE-TLIF arm at a 1:1 ratio and receive treatments at the Third Affiliated Hospital of Sun Yat-sen University. A diagram of the trial design is shown in figure 1. The primary outcome is the Oswestry Disability Index (ODI) score at 1-year postoperation. The study has been registered and can be accessed online on the China Clinical Trial Registration Center website (https://www.chictr.org.cn/), with the registration date being 14 March 2023. Trial registration data of this study is in online supplemental table 1.

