### Sample size

The MCID for ODI scores reported in similar studies is 8–12.^22 23^ After discussing among experienced professors from the spine surgery department, 8 in ODI score is chosen as the margin of non-inferiority (ðN) in this study. Based on the Consolidated Standards of Reporting Trials 2010 statement,^28^ it is assumed that the expected response is the same in both groups, the estimated true difference between the two surgeries is 0, and the ðN is 8. The SD is estimated to be 13 based on previous studies.^29^ The test level is one sided (α=0.025), and the test power (1−β) is 0.8. Considering that 10% of population may loss to follow-up, a total of 96 subjects are required in this clinical study.

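### The full analysis set is limited to complete data while missing values are imputed, and a 90% quota leaves per-protocol membership undetermined

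*Protocol article*

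**What the plan says.** All the relevant text is in the protocol article.

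- **Full analysis set** (Statistical analysis): "all participants who were randomised to the surgical intervention and for whom complete data sets were accessible after randomisation".
- **Missing data** (Statistical analysis, next sentence): "In instances of missing data, we employed the last observation carried forward and baseline observation carried forward methods for imputation". It does not say which method applies when, or to which set.
- **Per-protocol set** (Statistical analysis): "For the per-protocol cohort, at least 90% of subjects should fulfil the following criteria". Four criteria follow: receipt of either operation, no protocol violation, and then "3) complete the full follow-up and (4) obtain all required data".
- **Planned loss** (Sample size): "Considering that 10% of population may loss to follow-up", leading to 96 patients.
- **Design and endpoint** (Study design and settings): "This is a prospective, randomised, controlled, non-inferiority clinical study"; "The primary outcome is the Oswestry Disability Index (ODI) score at 1-year postoperation".
- **Rescue of the endpoint** (Primary outcome): a patient who does not return in the 12 to 15 month window is telephoned to complete the ODI. The Secondary outcome section allows phone or email for questionnaires.

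**The concern.** Two stated rules conflict, and a third cannot be applied.

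A set restricted to patients with complete data contains nothing to impute. The PP set cannot use the imputation either, because its last two criteria demand full follow-up and all required data. Taken literally, the imputation rule serves neither efficacy set.

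The PP sentence opens with a proportion of a group. That does not tell an analyst whether a given patient is in or out, so two analysts could build different PP sets from the same data.

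This matters more in a non-inferiority trial, where the two analyses are meant to check each other. If both leave out patients with missing data, neither shows what happens when loss to follow-up is related to outcome.

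**Working it through.** **1. The plan's own sample size.** Inputs from Sample size: margin 8, SD 13, true difference 0, one-sided α 0.025, power 0.80, loss 10%.

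- Normal approximation: n per arm = 2 × [13 × (1.960 + 0.842) / 8]² = 41.5, so 42. Then 42 / 0.9 = 46.7, so 47 per arm and 94 in total.
- With the t distribution: 43 per arm. Then 43 / 0.9 = 47.8, so 48 per arm and 96 in total.

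The stated 96 reproduces and is not in question.

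**2. The FAS and imputation sentences side by side.** If the FAS holds only complete cases, nothing in it is missing. If values are imputed, the FAS is not limited to complete cases. No other section gives a second definition that settles it.

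**3. A patient caught by the literal reading.** Table 2 schedules disc height, lordosis and fusion at day 360. The Radiological indicators section takes these from X-ray and CT, which a telephone call cannot supply. A patient reached only by telephone therefore has a valid primary outcome but an incomplete data set. That patient is outside the FAS and also fails the fourth PP criterion.

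**4. Effect on numbers.** With 10% loss, 96 × 0.9 = 86.4, so about 86 patients (43 per arm) have 1-year data; t-based power is then about 80.5%. Keeping all 96 (48 per arm) gives about 84.7%, assuming that the SD stays at 13 and imputation changes nothing else.

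**5. The 90% figure as a condition on all 96.** This is one reading only. The threshold is 0.9 × 96 = 86.4, so at least 87 patients must qualify. Let X be the number qualifying, binomial (96, p), with patients independent:

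| Proportion qualifying, p | P(X ≥ 87) |
|---|---|
| 0.90 (planned loss only) | 0.505 |
| 0.85 (assumed) | 0.075 |
| 0.95 (assumed) | 0.978 |

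At the planned loss the condition is unmet with probability 1 − 0.505 = 0.495, before any protocol violation is counted.

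**6. Bias from leaving out dropouts.** Suppose dropouts score D points worse at 1 year than completers. An arm's completer mean then understates its all-patient mean by (dropout proportion × D). The bias in favour of UBE-TLIF is (dropout in UBE-TLIF − dropout in MT-TLIF) × D. The protocol gives neither D nor arm-specific dropout, so all rows are assumptions; each averages the planned 10%.

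| UBE-TLIF v MT-TLIF dropout | D | Bias (ODI points) | Share of margin 8 |
|---|---|---|---|
| 10% v 10% | 20 | 0 | 0% |
| 12% v 8% | 20 | 0.04 × 20 = 0.8 | 10% |
| 15% v 5% | 10 | 0.10 × 10 = 1.0 | 12.5% |
| 15% v 5% | 20 | 0.10 × 20 = 2.0 | 25% |
| 5% v 15% | 20 | −2.0 | 25%, against UBE-TLIF |

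**The case against.** The strongest reply is that this is loose wording. The imputation sentence directly follows the FAS definition and is useless for the PP set, so the sponsor may well intend an imputed FAS of all randomised patients. That is plausible, but the text says the opposite and nothing elsewhere corrects it. Even on that intent, two imputation methods are named with no rule for choosing between them.

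Other objections succeed against stronger readings that a reader might infer:

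- **That the trial has no intention-to-treat analysis.** This follows only if the imputation sentence is ignored. The documents support a contradiction, not a settled completer analysis.
- **That the two sets must agree.** They need not. A protocol violator with complete data stays in the FAS and leaves the PP set. What is lost is the check on missing data, not the check on deviations.
- **That the PP set has no patient-level rule.** The four criteria are patient-level. The fault is the proportion placed in front of them.
- **That the 90% condition will probably fail.** The protocol names neither 96 as the denominator nor a consequence of falling short. If the phrase means that up to 10% non-compliers are tolerated, the binomial calculation does not apply. The result near one half also follows from setting the threshold at the expected value; its message is only that planned loss uses up the whole allowance.
- **That the result is biased towards UBE-TLIF.** Nothing in the protocol predicts more dropout in that arm.
- **That non-attendance means a missing primary outcome.** Telephone completion reduces missing ODI. It does not help if patients without imaging are then excluded.

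It can also be said that the content of the required data may be left to an analysis plan. That is fair for the detail, but not for rules in the article that conflict as stated.

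**Conclusion.** The point holds as a defect in stated definitions. The FAS and imputation sentences cannot both be followed, and PP membership cannot be determined from the sentence given. On the literal reading, both sets exclude patients with missing data, including some with a valid 1-year ODI, so their comparison gives no protection against informative dropout.

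The size is conditional. Within the scenarios shown, the bias runs from −2 to +2 ODI points, is zero when dropout is equal, and rests wholly on assumed dropout rates and deficits. The roughly even chance of missing 90% applies only if that figure is a condition on all 96 patients. The sample size stands.

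**What to change.** Amend the Statistical analysis section before the grouping information is released to the analysts:

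1. **FAS:** all randomised patients, analysed in the assigned arm, whether or not their data are complete.
2. **Missing 1-year ODI:** one named method for the primary analysis, in place of two without a rule for choosing. Any other method becomes a labelled sensitivity analysis.
3. **PP set:** each patient who received the assigned operation, had no major protocol violation and has a 1-year ODI. The present first criterion is met by either operation, whichever was assigned.
4. **Delete** the 90% quota and the requirement for all required data.
5. **Report** the primary non-inferiority comparison in both sets.

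The cost is wording and a little more analysis work. No further patients or visits are needed.

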### Outcome measurements

#### Primary outcome

The main outcome of the study is the ODI score at 1-year postoperation, which is a 10-item questionnaire specific to low back pain patients, including pain intensity, personal care (washing, dressing etc), lifting, walking, sitting, standing, sleeping, sex life (if applicable), social life and travelling. Each of the 10 items is scored from 0 to 5. Total scores are calculated by dividing the actual by the maximum score of 50 and converting it to a percentage. The score of 100% is recognised as the highest score, signifying the greatest dysfunction severity.^19 20^

The minimal clinically important difference (MCID) is a threshold value that patients and clinicians perceive as clinically meaningful. The clinically acceptable MCID in reported ODI scores is 8–12. However, to date, there is no consensus on calculating the optimal MCID for the ODI scores in groups.^21^,^23^ Consequently, following discussion, we adopted 8 as the MCID within clinically acceptable range. By comparing the ODI score 1 year after surgery, we can determine whether UBE-TLIF is not inferior to MT-TLIF within the non-inferiority margin of 8.

Considering that the condition of most enrolled subjects will be stabilised at 1-year postoperation, the assessment time frame of 1-year ODI is between 12 and 15 months after the operation. In case subjects do not return to the hospital for follow-up on time during this period, a telephone follow-up will be conducted to complete the ODI questionnaire.

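### Carrying baseline ODI forward leans towards non-inferiority when loss is equal in the two arms. A missing-at-random analysis should be primary, and the full analysis set must be reconciled with imputation.

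*Protocol article*

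**What the plan says.** The primary endpoint is fixed under Primary outcome: "The main outcome of the study is the ODI score at 1-year postoperation". A higher score is worse. Under Sample size, "8 in ODI score is chosen as the margin of non-inferiority", "the estimated true difference between the two surgeries is 0", and "The SD is estimated to be 13 based on previous studies". The same section sets a one-sided level of 0.025, power of 0.8, an allowance of 10% for loss to follow-up, and 96 patients in total.

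Under Statistical analysis, continuous variables, ODI among them, are compared by an independent t-test. For missing values, "we employed the last observation carried forward and baseline observation carried forward methods for imputation". That section also limits the full analysis set to randomised participants "for whom complete data sets were accessible after randomisation".

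Table 2 schedules ODI at baseline and at 1, 3, 6 and 12 months. Primary outcome allows the 1-year score to be taken between 12 and 15 months, by telephone if the patient does not attend.

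**The concern.** BOCF scores an operated patient as though surgery had changed nothing. Randomisation makes the baseline means equal in expectation, so putting baseline values into both arms at the same rate pulls the arm means together. In a superiority trial that is usually conservative. In a non-inferiority trial it works in favour of the new procedure. Baseline values also lie far from 1-year values, so mixing the two widens the SD and costs power. The t-test takes no account of the imputation.

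The analysis set is a separate contradiction. If membership requires complete data, there is nothing to impute. If values are imputed, membership cannot require complete data. At stake are the error rate and the power of the primary conclusion.

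**Working it through.** **1. The plan's own figure.** n per arm = 2 × 13² × (1.960 + 0.842)² / 8² = 41.5, so 42. The t-based version needs 43 (power 0.805), and 43/0.9 = 47.8, so 48 per arm and 96 in total. The stated size is reproduced. With 48 per arm and nothing missing, power is 0.847.

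**2. Fair reference.** With 10% missing at random and observed values only (about 43 per arm), error is about 2.5% (simulated 2.6%) and power about 81%.

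**3. Assumptions.** The article gives no ODI levels. I take 45 at baseline and 18 at 1 year (a gap of 27), with a range from 40/20 to 55/18. The SD is 13 at both times, the correlation in the simulations is 0.3, there are 48 per arm, and missingness is unrelated to outcome.

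**4. All missing values filled by BOCF, 10% per arm.**
- Mean difference under a true deficit of 8: 0.9 × 8 = 7.2.
- Variance in an arm with gap g: 13² + 0.1 × 0.9 × g².
- Power (true difference 0, g = 27 in both arms): variance 169 + 65.6 = 234.6, SD 15.3, SE = 15.3 × √(2/48) = 3.13. Then 8/3.13 − 1.96 = 0.60, which gives 72.5%. Simulated: about 72% (62–77% over the range).
- Error (true difference 8, so g = 27 in MT-TLIF and 19 in UBE-TLIF): variances 234.6 and 201.5, pooled SD 14.8, SE 3.01. Then (8 − 7.2)/3.01 − 1.96 = −1.69, which gives 4.5%. Simulated: about 4.2% (3.8–4.6% over the range).

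The rise in error comes from the shrinkage. The wider SD slightly offsets it.

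**5. LOCF alone, 10% per arm, carried value 0–5 points from the 1-year value.**
- The SD is 13.0–13.1 and power about 85%.
- If the earlier arm difference equals the 1-year difference, error stays at 2.5%.
- If it is half, the difference becomes 0.9 × 8 + 0.1 × 4 = 7.6 and error is about 3.5%.

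**6. BOCF only where no post-operative score exists.** Assume 2% BOCF and 8% LOCF per arm, with the carried score 3 points worse than at 1 year.
- Same earlier difference: 0.98 × 8 = 7.84, error about 2.7%.
- Half the earlier difference: 7.2 + 0.08 × 4 = 7.52, error about 3.5%.
- Power is about 82% in both cases.

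**7. Unequal loss, all BOCF, gap 27.**

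| Missing UBE / MT | Mean difference at true 8 | Error | Mean difference at true 0 | Power |
|---|---|---|---|---|
| 5% / 15% | 7.6 + 0.05 × 27 − 0.15 × 27 = 4.9 | 16% | −2.7 | 93% |
| 15% / 5% | 6.8 + 0.15 × 27 − 0.05 × 27 = 9.5 | 0.7% | 2.7 | 39% |

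Error and power move together, and the direction depends on which arm loses more.

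**The case against.** The strongest reply is that pure BOCF is unlikely. With ODI scheduled at 1, 3 and 6 months, most patients who miss the 1-year score will have a post-operative value to carry, and a natural reading uses BOCF only when there is none. The article does not state this reading, but on it the effect is small (step 6). The wider window and telephone completion may also hold missingness below the 10% allowed for. The per-protocol set requires complete follow-up and so needs no imputation, which gives a partial check, although the article does not say which set is primary. All of this stands. It limits the size of the problem but does not make carry-forward a good primary method.

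A reader might go further in four ways that the documents do not support:
- **LOCF and BOCF do the same harm.** They do not. LOCF from a stable score adds almost no variance and costs no power.
- **Error of 16% or power of 39% is to be expected.** Those figures need a threefold imbalance in loss together with pure BOCF. Nothing in the article points to such an imbalance, and patients are meant not to know which procedure they had.
- **The power loss is 13 points, from 85% to 72%.** The 85% assumes nothing missing. Against observed values only (81%), the loss is about 9 points.
- **Having no rule for which method applies to whom is itself an error.** That detail is commonly left to the statistical analysis plan, which is not shown.

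**Conclusion.** The point holds in limited form. The article fixes a carry-forward method that leans towards non-inferiority under equal loss. At 10% missing per arm, error is about 4.2% and power about 72% if everything is filled by BOCF, and about 2.7–3.5% and 82% if BOCF is the exception. An analysis of observed values gives about 2.5% and 81%. With unequal loss under BOCF, the bias follows the arm that loses more.

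The sizes rest on assumed ODI levels, on missingness unrelated to outcome, and on the 10% rate. The direction under equal loss requires only that the baseline means are equal in expectation. The conflict between the full-analysis-set definition and the imputation sentence needs no assumption. The planned 96 patients are not affected.

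**What to change.** 1. Make a missing-at-random analysis primary for 1-year ODI: either a mixed model on ODI at 1, 3, 6 and 12 months with baseline ODI, or multiple imputation from the same visits.
2. Add a delta-adjusted sensitivity analysis that worsens imputed UBE-TLIF values in steps up to the margin of 8, and report where the conclusion changes.
3. Keep LOCF and BOCF at most as labelled sensitivity analyses.
4. Redefine the full analysis set so that it does not require complete data, in line with the imputation sentence.

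The cost is revised wording and slightly more programming. All the visits are already scheduled, so no new data and no change to the sample size are needed.

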### Randomisation

A randomised block design will be adopted with admission time being the matching factor. Specifically, four adjacent patients who are admitted in the same month will be considered as a block. Within each block, the four subjects can be arranged in six distinct permutations: AABB, ABAB, ABBA, BAAB, BABA and BBAA, corresponding to the random numbers 1–6, respectively. These permutations are then randomly assigned to two groups, designated as group A and B. Following the determination of the arrangements, the subsequent phase entails a random selection from the six pre-established sequences. For each selection, a number is randomly drawn from the set ranging from 1 to 6. For example, the selection of the number 5 is specifically designated to represent the ‘BABA’ arrangement. The four subjects who enter this block are assigned to groups B, A, B and A, respectively. Random numbers ranging from 1 to 6 will be generated by a research assistant, who is blinded to the trial, using a personal computer prior to the commencement of patient recruitment. Subsequently, the random numbers will be concealed in sequentially coded, opaque and sealed envelopes and opened by another research assistant.

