### Baseline data

Baseline data including demographics, comorbidity, ODI score, Visual Analogue Scale (VAS) score, 36-Item Short Form Survey (SF-36) and EuroQol 5 Dimensions (EQ-5D) questionnaire will be collected. X-rays that measure the DH of operated level and lumbar lordosis (LL) angles will be conducted. DH can be calculated as the average value of the height from anterior part, middle part and posterior part in the same disc. LL angle is defined as the angle between the upper endplate of vertebra Lumbar one and Sacral 1.^15^,^17^

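### The 1-year ODI is to be compared by an unadjusted t-test although baseline ODI is collected: a valid test, but one that gives up precision

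*Protocol article*

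**What the plan says.** The Primary outcome section defines the endpoint: "The main outcome of the study is the ODI score at 1-year postoperation". The Sample size section sets the yardstick: "8 in ODI score is chosen as the margin of non-inferiority".

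The Statistical analysis section groups ODI with the other continuous measures ("Continuous variables, including VAS score, ODI score, operation time, intraoperative blood loss") and assigns one method to the whole group: "The independent t-test and Pearson χ^2^ will be applied to analyse continuous and categorical variables, respectively". The sentence is not labelled as the primary analysis, but the article gives no other method for the primary outcome. It mentions no covariate, change score, ANCOVA, mixed model or block term.

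Baseline ODI is part of the planned data: "Baseline data including demographics, comorbidity, ODI score, Visual Analogue Scale (VAS) score". Table 2 schedules it before surgery for every patient, along with VAS, the SF-36 scales, EQ-5D, disc height and lordosis.

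The Randomisation section describes blocking on admission time: "A randomised block design will be adopted with admission time being the matching factor", where "four adjacent patients who are admitted in the same month will be considered as a block".

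**The concern.** A baseline measure of the primary outcome usually explains part of the variation in the follow-up score. An analysis that leaves it out has a wider confidence interval than the same patients could provide. In this trial the conclusion rests on whether the upper confidence limit lies below a fixed margin of 8, so interval width bears directly on the chance of success. The sample size also has little reserve: 43 completers per arm just reach 80% power and 42 fall just short.

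Allocation is balanced on admission time and not on baseline severity, so the arms may differ by chance in baseline ODI. An unadjusted comparison does nothing about such a difference once it is seen. Naming the covariate in advance also removes the temptation to decide on adjustment after looking at the baseline table.

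**Working it through.** **Inputs from the Sample size section:** margin 8, SD 13, true difference 0, one-sided α 0.025, power 0.80, dropout 10%, total 96. The 1:1 allocation is in Study design and settings.

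**Assumptions, not in the document:** the correlation r between baseline and 1-year ODI, shown from 0.1 to 0.5; and that SD 13 is the SD of raw 1-year scores, which the article does not say.

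**1. Reproduce the plan's figure.**
- Normal approximation: n per arm = 2 × (1.96 + 0.8416)² × 13² / 8² = 41.5, so 42. Then 42 / 0.9 = 46.7, so 47 per arm and 94 in total.
- Noncentral t: 42 per arm gives 79.6% power and 43 gives 80.5%, so 43 are needed. Then 43 / 0.9 = 47.8, so 48 per arm and 96 in total.

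The stated 96 is reproduced exactly by the t-based calculation, with no use of a baseline correlation.

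**2. Unadjusted analysis at 43 completers per arm.**
- Standard error = 13 × √(2/43) = 2.80.
- Noncentrality = 8 / 2.80 = 2.85; power 80.5%.
- 95% CI half-width = 1.989 × 2.80 = 5.58 points.

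**3. Add baseline ODI as a covariate.** Residual SD = 13 × √(1 − r²). One degree of freedom is lost (86 − 3 = 83). The last column is 1 / (1 − r²), the equivalent multiple of the sample size.

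| r (assumed) | Residual SD | Power | CI half-width | Equivalent sample size |
|---|---|---|---|---|
| 0 (t-test) | 13.00 | 80.5% | 5.58 | 1.00 |
| 0.1 | 12.93 | 80.9% | 5.55 | 1.01 |
| 0.2 | 12.74 | 82.1% | 5.46 | 1.04 |
| 0.3 | 12.40 | 84.0% | 5.32 | 1.10 |
| 0.4 | 11.91 | 86.8% | 5.11 | 1.19 |
| 0.5 | 11.26 | 90.3% | 4.83 | 1.33 |

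**4. The block factor.** A simulation used 24 blocks of four (96 patients) and 20,000 runs per setting, with an assumed share of outcome variance lying between blocks. It compared the t-test with a model that has fixed block effects.

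| Between-block share (assumed) | Power, t-test | Power, block model | One-sided error, t-test (nominal 0.025) |
|---|---|---|---|
| 0 | 84.7% | 84.4% | 0.025 |
| 0.02 | 84.8% | 85.1% | 0.024 |
| 0.05 | 85.5% | 86.4% | 0.022 |
| 0.10 | 85.9% | 87.9% | 0.020 |

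Over this range, fixed block terms change power by between −0.3 and +2 points. Leaving them out makes the t-test slightly conservative.

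**The case against.** The strongest reply is that nothing here is wrong. In a randomised trial the unadjusted t-test is unbiased and holds its error rate, it matches the sample-size calculation, and it reaches the planned power. The sentence is a one-line summary that also covers outcomes with no baseline value, such as operation time and blood loss, and covariates are often left to a statistical analysis plan, which may exist. The gain rests on a correlation that the document does not supply, and at r = 0.1 it is negligible.

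Most of this stands, and it limits the point to an improvement. It does not remove the point, because the article names a method for ODI, and that method makes no use of a baseline value the trial already collects.

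A reader might infer three stronger things that the document does not support.

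- **That the trial is underpowered or the test invalid.** Step 1 shows otherwise.
- **That chance baseline imbalance biases the result.** If the baseline SD were also 13 (assumed), the standard error of the baseline difference at 48 per arm would be 13 × √(2/48) = 2.65, and a difference of 4 points or more in either direction would arise about 13% of the time. At an assumed slope of 0.4 it would move the estimate by 4 × 0.4 = 1.6 points, a fifth of the margin. That is ordinary sampling error, already covered by the t-test's confidence interval.
- **That ignoring the blocks is a serious fault, or that modelling them costs nothing.** The effect is small and conditional on outcomes drifting with admission time, which the article gives no reason to expect. The error is in the cautious direction for a non-inferiority claim, and 24 fixed block effects use 23 degrees of freedom.

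**Conclusion.** The point holds as one of lost precision. The article fixes an unadjusted comparison of 1-year ODI while collecting the most obvious covariate. The gain forgone runs from negligible (about 81% power at r = 0.1, against 80.5%) to moderate (about 90% at r = 0.5). These figures assume 43 completers per arm and an SD of 13 that refers to raw 1-year scores. The correlation itself is unknown, so the direction of the benefit is more certain than its size. The sample size of 96 needs no change, and the block factor is a minor, optional matter.

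**What to change.** Before unblinding, name one primary model: ANCOVA of 1-year ODI on arm and baseline ODI. Report the adjusted difference, UBE-TLIF minus MT-TLIF, with its two-sided 95% CI, and conclude non-inferiority if the upper limit is below 8. Keep the independent t-test as a sensitivity analysis. Use the same baseline adjustment for VAS, SF-36, EQ-5D, disc height and lordosis. Outcomes without a baseline value can stay as planned.

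If the blocked randomisation is to be reflected, a coarse admission-period term is enough. Whether it is included should be fixed in advance.

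The cost is one baseline covariate, one degree of freedom and a change of wording in the analysis plan. No further patients, visits or data are needed.
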